## Abstract

**Background:**

Diabetes is an important contributor to the burden of disease in South Africa and prevalence rates as high as 33% have been recorded in Cape Town. Previous studies show that quality of care and health outcomes are poor. The development of an effective education programme should impact on self-care, lifestyle change and adherence to medication; and lead to better control of diabetes, fewer complications and better quality of life.

**Methods:**

**Trial design:** Pragmatic cluster randomized controlled trial

**Participants:** Type 2 diabetic patients attending 45 public sector community health centres in Cape Town

**Interventions:** The intervention group will receive 4 sessions of group diabetes education delivered by a health promotion officer in a guiding style. The control group will receive usual care which consists of ad hoc advice during consultations and occasional educational talks in the waiting room.

**Objective:** To evaluate the effectiveness of the group diabetes education programme

**Outcomes:** Primary outcomes: diabetes self-care activities, 5% weight loss, 1% reduction in HbA1c. Secondary outcomes: self-efficacy, locus of control, mean blood pressure, mean weight loss, mean waist circumference, mean HbA1c, mean total cholesterol, quality of life

**Randomisation:** Computer generated random numbers

**Blinding:** Patients, health promoters and research assistants could not be blinded to the health centre’s allocation

**Numbers randomized:** Seventeen health centres (34 in total) will be randomly assigned to either control or intervention groups. A sample size of 1360 patients in 34 clusters of 40 patients will give a power of 80% to detect the primary outcomes with 5% precision. Altogether 720 patients were recruited in the intervention arm and 850 in the control arm giving a total of 1570.

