### Aim and objectives

Aim: To evaluate, by means of a pragmatic cluster randomized controlled trial, the effectiveness of a group diabetes education programme delivered by trained health promoters with a guiding (motivational interviewing) style, in community health centres in Cape Town, South Africa.

Objective 1: To evaluate effectiveness by assessing group changes in the following:

*Primary outcomes:* improved diabetes self-care activities, 5% weight loss, HbA1c reduction of 1 percentage point

*Secondary outcomes:* improved diabetes-specific self-efficacy, locus of control, mean blood pressure, mean weight loss, mean waist circumference, mean HbA1c, mean total cholesterol and quality of life

Objective 2: To evaluate fidelity to the educational programme and motivational interviewing by use of audiotapes and scoring health promoters with the Motivational Interviewing Integrity Code.

Objective 3: To explore the experiences of the health promoters with regards to their training and delivery of the diabetes education programme.

Objective 4: To explore the experiences of patients who attend the diabetes education sessions.

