### Sample size

Data from a previous study in the same population (n=450, 18 clinics) showed that the mean HbA1c was 8.8% (SD 3.3) and intraclass correlation 0.1
[22]. Similarly the mean weight was 78.2Kg (SD 16.7) and intraclass correlation 0.05. These figures were used to calculate the sample and cluster size for a 5% weight reduction and a 1% reduction in HbA1c. Based on a level of significance of 0.05 and a power of 0.8 the study required 17 clusters in each arm with 40 patients per cluster. The total sample size therefore would be 34 clusters (health centres) and 1360 patients.

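### The abstract's 80% power is attributed to all three primary outcomes, but the reported sample-size calculation covers only weight and HbA1c, so the figure is unsupported for self-care

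*Protocol article*

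**What the plan says.** The abstract gives the outcomes as "Primary outcomes: diabetes self-care activities, 5% weight loss, 1% reduction in HbA1c", and the Aim and objectives section repeats the same three: "improved diabetes self-care activities, 5% weight loss, HbA1c reduction of 1 percentage point". Neither place ranks them. The abstract then says, with no exception for any of the three: "A sample size of 1360 patients in 34 clusters of 40 patients will give a power of 80% to detect the primary outcomes".

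The Sample size section supplies two sets of inputs: "the mean HbA1c was 8.8% (SD 3.3) and intraclass correlation 0.1", and "Similarly the mean weight was 78.2Kg (SD 16.7) and intraclass correlation 0.05". It states what they were for: "These figures were used to calculate the sample and cluster size for a 5% weight reduction and a 1% reduction in HbA1c". The error level and power are set out as "Based on a level of significance of 0.05 and a power of 0.8". The conclusion that the section draws from all this is that "the study required 17 clusters in each arm with 40 patients per cluster". Whether the test is one- or two-sided is not said.

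Self-care is absent from that section. The Data collection tools section describes its questionnaire as scoring five domains separately. It names no composite score, no single domain as the endpoint and no threshold for improvement.

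**The concern.** The abstract makes a positive claim that the body of the article does not bear out. Shortening does not explain this, because the Sample size section itself names the two outcomes that its figures served.

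What is at stake is how a null self-care result would be read. The article says that the trial is meant to help policy makers decide on wider implementation. A reader who relies on the abstract could take a null self-care result as a negative finding from a trial with 80% power for that outcome. Nothing in the article supports that reading.

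**Working it through.** **1. Does the stated sample size need a self-care input?**

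Inputs from the Sample size section: HbA1c SD 3.3, ICC 0.1, difference 1 percentage point; weight mean 78.2 kg, SD 16.7, ICC 0.05, difference 5% of 78.2 = 3.91 kg; significance level 0.05; power 0.8; 40 patients per cluster. Both outcomes are treated as differences in means, since an SD and an ICC are what the article gives.

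Patients per arm without clustering: n = 2(z_α + z_β)² SD²/δ². Design effect: DE = 1 + (40 − 1) × ICC, which is 4.90 for HbA1c and 2.95 for weight. Clusters per arm = n × DE/40, rounded up.

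| Outcome | Test at 0.05 | n | n × DE | Clusters per arm | Total patients |
|---|---|---|---|---|---|
| HbA1c | one-sided | 135 | 661.5 | 16.5 → 17 | 1360 |
| Weight | one-sided | 226 | 666.7 | 16.7 → 17 | 1360 |
| HbA1c | two-sided | 171 | 837.9 | 20.9 → 21 | 1680 |
| Weight | two-sided | 287 | 846.7 | 21.2 → 22 | 1760 |

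The stated 17 clusters per arm and 1360 patients are reproduced from each of the two outcomes with a one-sided 0.05 test. No self-care input is needed.

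**2. Power of 17 × 40 = 680 per arm for those two outcomes**

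Standard error in SD units: SE = √(2 × DE/680). Power = Φ(δ/(SD × SE) − z_α).

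- HbA1c: 1/3.3 = 0.303; SE = √(9.80/680) = 0.120; ratio 2.52. Two-sided: Φ(2.52 − 1.96) = 71%. One-sided: Φ(2.52 − 1.645) = 81%.
- Weight: 3.91/16.7 = 0.234; SE = √(5.90/680) = 0.0931; ratio 2.51. Two-sided: 71%. One-sided: 81%.

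The numbers actually recruited (720 and 850, taken as 17 centres per arm) change little: two-sided power is 72% for HbA1c and 73% for weight, before any loss to follow-up.

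**3. Can a power for self-care be worked out?**

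Not from the article. It would need a target difference, an SD and an ICC for at least one domain score, and none is given. The table below is an illustration only. It treats one domain score as continuous and uses a two-sided 0.05 test. The ICCs and the effects of 0.2 and 0.3 SD are assumptions; 0.05 and 0.10 are borrowed from weight and HbA1c. The detectable difference is (1.960 + 0.842) × SE.

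| Assumed ICC | SE | Detectable at 80% power | Power at 0.2 SD | Power at 0.3 SD |
|---|---|---|---|---|
| 0.01 | 0.0639 | 0.18 SD | 88% | 99.7% |
| 0.05 | 0.0931 | 0.26 SD | 57% | 90% |
| 0.10 | 0.1200 | 0.34 SD | 38% | 70% |

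One-sided, the detectable differences are 0.16, 0.23 and 0.30 SD. Power falls on both sides of 80% within this small grid.

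**The case against.** Four points can be made against the concern.

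*The Sample size section is open about its scope, so the fault is one loosely condensed sentence.* This stands as a limit on seriousness. It does not remove the mismatch, because the abstract is what many readers will rely on.

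*The full protocol is not shown and may hold a self-care calculation.* This also stands in part. The article shows only that it reports no self-care inputs and names two other outcomes as the basis of the sample size. It cannot prove that no such calculation exists elsewhere.

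*A reader might infer that the trial is underpowered for self-care.* The documents do not support this. The low figures of 57% and 38% depend on an effect of 0.2 SD that has no source in the article. At 0.3 SD, close to the standardised HbA1c target of 0.303, power runs from 70% to 99.7%. With an ICC of 0.10 and that same standardised effect, a self-care score would have exactly the power that HbA1c has. The illustration also ignores the planned adjustment for baseline covariates, which would usually reduce the standard error. That self-care is listed first carries no weight either, as the primary outcomes are not ranked.

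*Limiting the 80% to weight and HbA1c would leave a figure that holds only one-sided.* This is right, and it shapes the correction. A one-sided 80% for two outcomes beside two-sided detectable differences for self-care would make self-care look worse for no reason but the change of basis.

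**Conclusion.** The point holds in a limited form. The abstract attributes 80% power to three primary outcomes, while the calculation that the article describes covers two. For self-care the figure has no stated basis, and none can be supplied from the article. This conclusion rests on comparing the sections and needs no assumption about effect or ICC.

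Whether the true power for self-care is above or below 80% is not known. The detectable differences of 0.18 to 0.34 SD are conditional on assumed ICCs of 0.01 to 0.10, a two-sided test and a single domain score; they are not properties of the design. For the two outcomes that were calculated, the stated power is met only with a one-sided 0.05 test (about 81%, against about 71% two-sided), with both taken as differences in means under a normal approximation.

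This is an inconsistency in a stated figure that should be corrected. It does not affect the validity of the trial.

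**What to change.** 1. Restrict the abstract's power sentence to HbA1c and weight and give its sidedness. For example: *with 17 clusters of 40 per arm, power is about 81% at a one-sided 0.05 level (about 71% two-sided) for a mean difference of 1 percentage point in HbA1c, and likewise for 3.91 kg in weight.*
2. State in the abstract and the Sample size section that no power was calculated for self-care. If the full protocol does hold such a calculation, report its target difference, SD and ICC for each domain score instead.
3. Interpret a null self-care result by its confidence interval, not as a negative result at 80% power.
4. If a detectable difference for self-care is quoted at all, label it illustrative, per domain score, conditional on an assumed ICC, and on the same sidedness as the figures for HbA1c and weight.

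The cost is a few sentences and a less favourable power statement. No patients, data or analyses change. The Timeline section says that analysis is under way, so the wording can still be settled before the results are interpreted.

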**Discussion:**

The study will inform policy makers and managers of the district health system, particularly in low to middle income countries, if this programme can be implemented more widely.

**Trial register:**

Pan African Clinical Trial Registry PACTR201205000380384

## Background

Diabetes is a significant contributor to the burden of disease in South Africa
[1] and the prevalence in Africa is expected to increase by 80% over the next 15 years
[2]. Self-reported prevalence rates for diabetes of 2.4% in men and 3.7% in women have been reported in South Africa
[3]. However, studies in the Western Cape, one of the nine provinces of South Africa, suggest rates in urban areas as high as 33%
[4].

Approximately 80% of the 3,1 million population in the Cape Town Metropole are uninsured and rely on public sector facilities to manage their diabetes. Several previous studies in the Western Cape have illustrated the poor quality of care and outcomes for diabetic patients
[5,6]. Almost 80% of patients were uncontrolled (HbA1c≥7%) in an audit of type 2 diabetes in Cape Town’s public sector in 2011
[6]. Deficiencies in knowledge and self-care amongst patients and the inability of primary care providers to ameliorate this, have been identified as part of the problem. The population served by the public sector is characterized by low socio-economic status, low levels of education and low health literacy. The population served come from historically disadvantaged communities and speak mainly Afrikaans or Xhosa.

Primary care services in the country are largely nurse-led with the support of doctors. Other health workers, appropriate to the management of diabetes, such as dieticians and podiatrists, are usually not available. A variety of mid-level workers, such as health promoters, have been trained and employed in community health centres. Currently the education of diabetic patients and support of self-care has been left to the varied initiatives of individual health workers and there is no structured programme of education for people with diabetes in the Western Cape. Chronic care teams have identified that the health promoter should be the key person in delivering such a programme
[7].

Community health centres in the Western Cape are usually found in larger metropolitan areas or rural towns. Diabetic patients are often seen in such large numbers that a specific day is set aside each week for them to attend a diabetic “club”. At a given health centre patients are usually scheduled to attend the “club” as a group and are given appointments to be seen for review every 3 months.

During 2006–2008 the investigators were involved in an appreciative inquiry project to improve the annual review of the diabetic patients in the Cape Town Metropole. During this project the quality of care in the annual audit in terms of assessment of HbA1c, serum creatinine and cholesterol, retinal screening, foot screening and calculation of body mass index significantly improved
[7]. At the end of this project staff articulated the need for a better approach to diabetes education and collaborated in designing the content of a more structured programme to be delievered by health promoters
[7].

Health promoters have a secondary school education up to at least Grade 8 and once employed have additional training in the knowledge and skills required to deliver health education messages and promote health. There are currently 120 health promoters in the Province and the policy of the Department of Health is to have a health promoter at every community health centre. A recent study showed that the current health promoters have a good knowledge of key diabetes education messages for patients
[8].

Although a variety of individual and group educational materials are available from non-government organizations and pharmaceutical companies, no materials are officially disseminated or recommended by the national or provincial Department of Health.

The relationship between health care provider and patient is recognized to have an important influence on patient understanding and adherence
[9]. Motivational interviewing has been recommended as a more skilful guiding approach to eliciting lifestyle change and promoting self-care
[10] and a recent systematic review concluded that it out-performs traditional advice-giving in 80% of studies
[11,12]. Professors [name] and [name] are members of the International Network of Motivational Interviewing Trainers and have experience with training and researching in this area
[10,13]. Studies of individually-delivered motivational interviewing for diabetic patients have produced promising results
[14,15]. A recent study of individual motivational interviewing for the prevention of diabetes also demonstrated a significant effect on achieving 5% weight loss
[16].

Group interactions have been found to be effective in diabetes education
[17] and local chronic care staff have indicated that this is the most practical approach in their very busy health centres
[7]. A systematic review of group education in diabetes concluded that “The results of the meta-analyses in favour of group-based diabetes education programmes were: reduced glycated haemoglobin at four to six months (1.4%; 95% confidence interval (CI) 0.8 to 1.9; P < 0.00001), at 12–14 months (0.8%; 95% CI 0.7 to 1.0; P < 0.00001) and two years (1.0%; 95% CI 0.5 to 1.4; P< 0.00001); reduced fasting blood glucose levels at 12 months (1.2 mmol/L; 95% CI 0.7 to 1.6; P < 0.00001); reduced body weight at 12–14 months (1.6 Kg; 95% CI 0.3 to 3.0; P = 0.02); improved diabetes knowledge at 12–14 months (SMD 1.0; 95% CI 0.7 to1.2; P < 0.00001) and reduced systolic blood pressure at four to six months (5 mmHg: 95% CI 1 to 10; P = 0.01). There was also a reduced need for diabetes medication (odds ratio 11.8, 95% CI 5.2 to 26.9; P < 0.00001; RD = 0.2; NNT = 5). Therefore, for every five patients attending a group-based education programme we could expect one patient to reduce diabetes medication”
[17]. Motivational interviewing in group format is a relatively new development; 12 published reports have emerged
[18,19], which include three randomized trials and one study in the diabetes field
[20].

Despite evidence of the effectiveness of group diabetes education all of the trials have been conducted in high-income countries and by health professionals such as doctors or nurses. This trial will be the first in an African context and delivered by mid-level health workers. In addition the incorporation of group motivational interviewing will add to a small evidence base on this topic.

If the study demonstrates effectiveness of this educational intervention then it can be implemented throughout the Western Cape and may well be replicated in the rest of the country and possibly within the southern African Region. The study intends to inform policy makers and managers of the district health services and help them decide whether to implement the programme more widely.

### Aim and objectives

Aim: To evaluate, by means of a pragmatic cluster randomized controlled trial, the effectiveness of a group diabetes education programme delivered by trained health promoters with a guiding (motivational interviewing) style, in community health centres in Cape Town, South Africa.

Objective 1: To evaluate effectiveness by assessing group changes in the following:

*Primary outcomes:* improved diabetes self-care activities, 5% weight loss, HbA1c reduction of 1 percentage point

*Secondary outcomes:* improved diabetes-specific self-efficacy, locus of control, mean blood pressure, mean weight loss, mean waist circumference, mean HbA1c, mean total cholesterol and quality of life

Objective 2: To evaluate fidelity to the educational programme and motivational interviewing by use of audiotapes and scoring health promoters with the Motivational Interviewing Integrity Code.

Objective 3: To explore the experiences of the health promoters with regards to their training and delivery of the diabetes education programme.

Objective 4: To explore the experiences of patients who attend the diabetes education sessions.

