### Inclusion and exclusion criteria

Inclusion: All type 2 diabetic patients who gave consent, regardless of the type of medication (oral and/or insulin) or time since diagnosis.

Exclusion: Type 1 diabetic patients, those who refused consent, those who were judged by the clinical nurse practitioner or medical officer as unable to participate in the intervention (for example due to acute illness, mental illness, dementia or another justifiable reason).

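### The 80% power claimed for the primary outcomes was calculated for differences in mean HbA1c and mean weight, which are listed as secondary; power for the apparent responder primaries is not given

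*Protocol article*

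**What the plan says.** Under Aim and objectives, the primary outcomes are "improved diabetes self-care activities, 5% weight loss, HbA1c reduction of 1 percentage point". The secondary list in the same section includes "mean weight loss, mean waist circumference, mean HbA1c, mean total cholesterol and quality of life". The abstract repeats the split.

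The Sample size section takes its inputs from an earlier study in the same population, which "showed that the mean HbA1c was 8.8% (SD 3.3) and intraclass correlation 0.1". It continues: "Similarly the mean weight was 78.2Kg (SD 16.7) and intraclass correlation 0.05". The purpose of these inputs is then given: "These figures were used to calculate the sample and cluster size for a 5% weight reduction and a 1% reduction in HbA1c". Alpha is set at 0.05 and power at 80%, from which the article concludes that "the study required 17 clusters in each arm with 40 patients per cluster"; this amounts to 34 clusters and 1360 patients. Whether the significance level is one- or two-sided is not stated.

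The abstract attaches 80% power at this size to the primary outcomes. The Data analysis section plans linear regression for continuous outcomes and logistic regression for categorical ones, both adjusted for baseline covariates and clustering. It does not assign individual outcomes to either model.

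**The concern.** If the weight and HbA1c primaries were mean differences, the secondary list would repeat them. The two lists are distinct only if the primaries are achieved-or-not thresholds for each patient. The inputs to the sample size are nevertheless means, SDs and intraclass correlations of continuous measurements. Nothing in the section describes how many patients in either arm are expected to reach a threshold.

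The outcomes that carry the power statement would then not be the ones named primary. The trial is meant to inform a decision on wider roll-out. A reader who sees a null responder result beside an 80% power claim could take it as well-powered evidence of no effect, and the article gives no basis for that.

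**Working it through.** **1. Reproducing the stated size.** Inputs from the Sample size section: HbA1c SD 3.3, ICC 0.1, difference 1.0; weight SD 16.7 kg, ICC 0.05, difference 5% × 78.2 = 3.91 kg; 40 patients per cluster; alpha 0.05; power 0.80.

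Patients per arm before clustering: n = 2(SD/δ)²(z_α + z_β)². Design effect: DE = 1 + 39 × ICC. Clusters per arm: n × DE / 40, rounded up.

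| | DE | One-sided 0.05 | Two-sided 0.05 |
|---|---|---|---|
| HbA1c | 4.9 | 135 × 4.9 / 40 = 16.5 → 17 | 171 × 4.9 / 40 = 20.9 → 21 |
| Weight | 2.95 | 226 × 2.95 / 40 = 16.7 → 17 | 287 × 2.95 / 40 = 21.2 → 22 |

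Both outcomes give the stated 17 per arm (2 × 17 × 40 = 1360) as a one-sided comparison of means. This confirms that means were what was sized.

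**2. Two-sided power for the means at 17 × 40 = 680 per arm.** SE = SD × √(2 × DE / 680).
- HbA1c: 3.3 × √(9.8 / 680) = 0.396; 1/0.396 = 2.52; Φ(2.52 − 1.96) = 71%.
- Weight: 16.7 × √(5.9 / 680) = 1.556; 3.91/1.556 = 2.51; Φ(2.51 − 1.96) = 71%.

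**3. Responder power for HbA1c.** The article gives no proportions, so these are assumptions: normally distributed changes; a true 1.0-point shift; no change on average in controls; SD 3.3 at both visits; baseline–follow-up correlation r; no loss to follow-up. The responder ICC is either 0.10 (the continuous value carried over) or about 0.06 (converted from 0.1 through a bivariate normal).

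SD of change = 3.3 × √(2(1 − r)). Control responders p₀ = Φ(−1 / SD of change); intervention responders p₁ = 0.5.

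At r = 0.5 the SD of change is 3.3 and p₀ = 0.381. With ICC 0.10, SE = √[(0.236 + 0.250) × 4.9 / 680] = 0.059; 0.119/0.059 = 2.01; power Φ(0.05) = 52%. With ICC about 0.06, SE = 0.050 and power is 67%.

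| r | Responders, unadjusted (ICC 0.10 to about 0.06) | Mean change, unadjusted (ICC 0.10) |
|---|---|---|
| 0.3 | 40–53% | 57% |
| 0.5 | 52–67% | 71% |
| 0.7 | 74–87% | 90% |
| 0.8 | 89–97% | 98% |

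**4. Weight on the same approach.** With SD 16.7, a 3.91 kg shift and ICC 0.05, responder power is 89% at r = 0.8 and 99% at r = 0.9.

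**5. Directly assumed proportions**, 680 per arm, two-sided (approximate power):

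| Responders, control vs intervention | ICC 0.01 | ICC 0.05 | ICC 0.10 |
|---|---|---|---|
| 5% vs 10% | 85% | 53% | 35% |
| 10% vs 20% | 99% | 86% | 65% |
| 20% vs 30% | 95% | 70% | 49% |

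**The case against.** **The responder reading is inferred.** The article does not speak of a proportion reaching the threshold, introduces its outcomes as group changes, and treats 5% and 1 point as target mean differences in the Sample size section. This stands as a limit on certainty. On the alternative reading, however, the primary and secondary lists overlap and the outcome definition still needs correcting.

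**A reader might infer that the trial is underpowered for its primary outcomes.** The documents do not support that. Power depends on responder rates, a binary ICC and a correlation that are not given, and at r = 0.8 both HbA1c and weight responders exceed 80%.

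**A reader might also think the cut costs far more than it does**, by setting an unadjusted responder test against a baseline-adjusted mean (83% at r = 0.5, so a gap of 16 to 31 points). That is not like for like, since baseline adjustment is planned for both kinds of model. With neither adjusted, the gap at r = 0.5 is 71% against 52–67%, or 4 to 19 points.

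**Responder outcomes are defensible in themselves.** The Background cites a trial that used 5% weight loss, managers can read a percentage easily, and the mean versions are kept as secondary, so the continuous information is not thrown away. Eligibility is deliberately broad: "All type 2 diabetic patients who gave consent, regardless of the type of medication". The audit cited in the Background implies that about 20% were already below 7%, and a 1-point fall is hard for them to reach. Such patients would also dilute a mean difference, so this is a reason to report both forms, not proof that the threshold is wrong.

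**Swapping the primaries now would carry its own risk.** Follow-up ended in December 2011, data collectors were not blinded, and the Timeline says analysis is under way. This stands.

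**Conclusion.** The point holds as a mismatch between the power statement and the outcomes it is attached to. The size is that of a one-sided comparison of means, with about 71% power if the test is two-sided. It says nothing about responders. The 80% claim is therefore unsupported for the weight and HbA1c primaries on the most natural reading of the outcome lists.

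How far responder power departs from 80% cannot be settled from the article. For HbA1c it ranges from about 40% to 97% over correlations of 0.3 to 0.8, given normal changes, SD 3.3, a 1-point shift and responder ICCs between about 0.06 and 0.10. It should be described as unknown, not as low. This should be fixed, but it does not invalidate the design.

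**What to change.** 1. In Aim and objectives, state that the two primaries are the proportions of patients with at least 5% weight loss and with an HbA1c fall of at least 1 percentage point at 12 months.
2. In the abstract and Sample size, limit the 80% claim to the mean differences of 1 point and 3.91 kg for which it was calculated, and state whether alpha is one- or two-sided. If two-sided, the figure is about 71%.
3. Add responder power under stated proportions and binary ICCs, as a range like those above.
4. Report the baseline- and cluster-adjusted mean differences in HbA1c and weight, already prespecified as secondary, next to the responder results.
5. Keep the present order of primary and secondary outcomes unless it is documented that no between-arm comparison has been seen; any change should then be dated and disclosed.

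The cost is a few sentences and a short calculation. Recruitment is complete and no new data are needed.
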